## Non-clinical and clinical information

### Non-clinical information

Based on the known role of PD-L1 in the suppression of T cell responses and the strong correlation between PD-L1 expression and prognosis in cancer, the blockade of the PD-L1/PD-1 interaction is viewed as a highly promising strategy for cancer immunotherapy (Topalian et al., 2012). Merck KGaA has developed a fully human IgG1 antibody (avelumab) with neutralizing activity against PD-L1. The non-clinical pharmacology investigations have shown that avelumab functionally enhances T cell activation in vitro and significantly inhibits the growth of PD-L1 expressing tumors in vivo. In agreement with the hypothesis that PD-L1 neutralization acts to release anti-tumor T cells from immune suppression, the anti-tumor effects of avelumab *in vivo* were found to be primarily mediated by CD8+ T cells, as highlighted by the observation that the *in vivo* depletion of this cell type was sufficient to completely abrogate anti-tumor activity.

Depletion of CD8+ T cells also eliminated the synergistic efficacy of avelumab when given in combination with radiotherapy, suggesting that this combination synergizes through cooperative immune-enhancing mechanisms. As a second mode of action, avelumab is capable of stimulating ADCC activity against PD-L1+ tumor cells *in vitro* and elimination of ADCC potential *in vivo* significantly reduced anti-tumor activity.

In summary, the available preclinical data demonstrate that avelumab is capable of inhibiting tumor growth in vivo when applied as a monotherapy and its efficacy can be further enhanced *via* combination with standard-of-care therapies. Avelumab has the potential to offer significant clinical benefits to cancer subjects through its ability to release anti-tumor CD8+ T cells from the suppressive effects of PD-L1 in the tumor microenvironment. The investigation of this agent in human clinical trials is therefore warranted.

Overall, the non-clinical safety profile established for avelumab is considered adequate to support the use of avelumab in the planned therapeutic indication in humans.

Additional information can be found in the Investigator’s Brochure.

### Clinical information

As of the date of avelumab’s IB (31 March 2017), there are no completed clinical trials to report. No clinical trial is conducted over avelumab in locally-advanced rectal adenocarcinoma. However, avelumab at a dose of 10 mg/kg once every 2 weeks has demonstrated meaningful clinical activity across various tumor types (lung cancer, ovarian cancer, gastric cancer, gastroesophageal junction cancer, urothelial carcinoma, mesothelioma, and adrenocortical carcinoma) and treatment settings. Across the aforementioned tumor types, responses with avelumab were typically observed early during treatment and appear durable in nature, including ongoing responses lasting > 1 year in several of the different cohorts. Overall, many responders were still experiencing ongoing response at the time of the data cutoff for the analysis.

As for safety data from subjects with different tumor types treated with avelumab, they suggest an acceptable safety profile of the compound. Most of the observed events were either in line with those expected in subjects with advanced solid tumors or with similar class effects of mAb blocking the PD-1/PD-L1 axis. Infusion-related reactions including drug hypersensitivity reactions and immune-mediated adverse reactions (immune-related pneumonitis, immune-related colitis, immune-related hepatitis, immune-related endocrinopathies (thyroid disorders, adrenal insufficiency, new onset type I diabetes mellitus, pituitary disorders), immune-related nephritis and renal dysfunction and other immune-related adverse events (AEs: myositis, myocarditis, Guillain-Barré syndrome, uveitis) have been identified as important risks for avelumab. The known and potential risks and benefits to the patient are further discussed in Section 9.2.

## Study rationale

### Clinical study rationale

The traditional treatment of locally-advanced but operable rectal carcinoma consists of a combination of peri-operative long-course chemoradiation therapy, or alternatively a short-course radiation therapy to be followed by a surgery (TME), then by adjuvant chemotherapy for 4 months (Benson AB et al., 2016). All randomized phase III clinical trials failed to answer the question of the efficacy of adjuvant chemotherapy to impact on the outcome as DFS or overall survival (OS) (Breugmon AJ et al., 2015). Also, there is a good correlation between the rate of pCR and OS (de Castro et al., 2012). In an attempt to increase pCR in rectal cancer, the strategy of total neoadjuvant therapy was adapted in many phase II trials with increasing pCR up to 38% and in many ongoing phase III trials (Garcia-Aguilar J et al., 2015).

In POLISH III, a randomized clinical trial, short-course radiation therapy followed by 3 cycles of FOLFOX was compared to the regular long course with chemotherapy in improving OS at 3 years. The newly supported published data were in favor of total neoadjuvant therapy with short-course followed by chemotherapy followed by surgery (Bujko K et al., 2016a; Bujko K et al., 2016b). Also, all ongoing trials including RAPIDO and OPERA trials are testing the same hypothesis with total neoadjuvant therapy but without using immunotherapy like avelumab (Nilsson PJ et al., 2013; Smith JJ et al., 2015).

In view of the above data, a phase II clinical study is highly required to evaluate the pCR rate following short-course radiation (5 days), then mFOLFOX-6 chemotherapy protocol combined with 10 mg/kg of avelumab (once every 2 weeks for 6 cycles) in patients with locall-advanced rectal adenocarcinoma before undergoing a TME.

### Primary endpoint rationale

The pathologic complete response (pCR) rate following pre-operative treatment has been shown to be a surrogate for DFS in locally-advanced rectal cancer (Mass M et al., 2010). The use of pCR as a primary endpoint with evaluation of biomarkers such as changes in PD-L1 expression, CD8+ cell-infiltration associated with therapy, will enable a rapid proof of concept. It will also enable feasibility assessment to test the hypothesis that the addition of avelumab to mFOLFOX-6 chemotherapy administered following short-course radiation for locally-advanced rectal cancer will improve the disease’s post-operative outcomes and provide the basis for the planning of future randomized studies.

### Neoadjuvant treatment rationale

The tolerance of pre-operative chemotherapy and the compliance are much better than post-operative therapy, and the need to achieve a more pathologic response rate prior to surgery may translate to an increase in survival. Also, of the combination approaches that have currently been explored for avelumab, chemotherapy with FOLFOX and radiation therapy showed the better tumor growth inhibition. In particular, radiation therapy was found to be a highly synergistic combination capable of causing complete regression of established tumors with the potential to generate anti-tumor immune memory. Additional information can be found in the Investigator’s Brochure.

### Short-course radiation therapy rationale

The use of short-course is intended to induce the inflammatory reaction and increase the immune-mediated reaction while the use of both oxaliplatin and avelumab will maintain the immune and anti-tumor effect which can translate into an increased pCR. Also, the NCCN guidelines for the management of locally-advanced disease included the option of a short-course chemo-radiotherapy (SCRT) as data show tumor down-staging with SCRT (NCCN, 2016; Nilsson PJ et al., 2013).

### Avelumab dose regimen rationale

A dose of 10 mg/kg of avelumab, IV, once every 2 weeks, was selected for the expansion cohorts of phase I trials, the phase II pivotal trial (EMR100070-003), and the ongoing phase III trials based on the preliminary pharmacokinetic (PK), target occupancy, and clinical safety data collected in the clinical trials (Heery CR et al., 2017; Investigator’s Brochure of avelumab, version 7 of 31 March 2017).

Indeed, avelumab 10 mg/kg once every 2 weeks has demonstrated meaningful clinical activity across various tumor types and treatment settings. Regardless of the tumor type, responses with avelumab were observed early during treatment and appear durable in nature, including ongoing responses >1 year in several of the cohorts. Overall, many responders were still having ongoing response at the time of database lock. Based on the above analyses, a dose of 10 mg/kg IV once every 2 weeks was considered to have a favorable risk benefit profile and thus represents an appropriate dose for the present study. Additional information can be found in the Investigator’s Brochure.

# STUDY OBJECTIVES

## Primary objective

The primary objective of the study is to evaluate the pathologic complete response (pCR) rate following short-course radiation then mFOLFOX-6/avelumab.

## Secondary objectives

The secondary objectives of the study are:

1. To identify the proportion of patients who remain progression free at 3 years.
2. To explore changes in PD-L1 expression and T-cell infiltration.
3. To evaluate the safety and tolerability of mFOLFOX-6/avelumab.
4. To assess the quality of life of the patients in a neoadjuvant setting with avelumab.

# STUDY DESIGN

## Design

This is an open-label, single-arm multicenter and stage-2 phase II study investigating short-course radiation therapy (25 Gy in 5 fractions), followed 2 weeks later by 6 cycles of mFOLFOX-6 chemotherapy plus avelumab (10 mg/kg) given every 2 weeks in a successive manner such that mFOLFOX is administered 30 minutes after avelumab has been administered in patients with locally-advanced, potentially resectable rectal adenocarcinoma (**Figure 1**).

No screening period is planned.

All chemotherapy agents will be taken intravenously (infusion) every 2 weeks for 6 cycles during the treatment period (12 weeks), or until intolerable toxicity or withdrawal of patient’s informed consent. TME will performed 2 to 3 weeks after the last cycle of chemotherapy plus avelumab, depending on the patient’s condition and laboratory exams.

Each patient will be followed up for 3 years after surgery.

No reference therapy or placebo will be used in the trial.

Written informed consent must be obtained before any study specific medical procedure is performed.

Figure 1 Study design

**Week 1, D1-D5**

Radiotherapy: 25 Gy in 5 fractions

**Week 2 ± 3 days, D10**

Sigmoidoscopy and biopsy (PD-L1 expression on tumor and infiltrating immune T cells, CD4+, CD8+ and CD3+ T cell infiltration†, and MSI‡)

**Week 16 or 17 ± 3 days**

(2-3 weeks after last cycle of chemotherapy + avelumab)

Surgery: total mesorectal excision

(open, laparoscopic or robotic)

+

Resected specimen: PD-L1 expression on tumor and infiltrating immune T cells, CD4+, CD8+ and CD45RO+ T cell infiltration†, and TRG*

**Week 3 ± 3 days**

**mFOLFOX-6:** Oxaliplatin 85 mg/m2 in a 2-hour infusion

Leucovorin 400 mg/m2 over 2 hours

by a 48-hour infusion of fluorouracil 2,400 mg/m**2**

+

**Avelumab** 10 mg/Kg every 2 weeks ± 3 days in a successive manner such that mFOLFOX is administered 30-minutes after avelumab has already been administered

(6 cycles, first administration at D15)

12 weeks

‡ The microsatellite instability (MSI or MMR status) is determined once on either the baseline biopsy or D10 biopsy.

## Endpoints

The primary endpoint is the proportion of patients who achieve a pathological complete response, defined as no viable tumor cells onthe resected specimen.

The secondary endpoints are:

1. Progression-free survival (PFS) at 3 years will be estimated with the Kaplan-Meier method and presented with the 95% confidence interval (CI).
2. Evaluation of response by obtaining Tumor Regression Grade (TRG).
3. Evaluation of biomarkers: CD4+, CD8+ and CD3+ T cell infiltration, and changes in PD-L1 expression.
4. Frequency, severity, and attribution of AEs related to avelumab in neoadjuvant setting.
5. Quality of life assessment using the questionnaire for the functional assessment of cancer therapy for patients with colorectal cancer (FACT-C, English version 4 of 16 November 2007 or Arabic version 4 of 03 September 2014).

TRG system aims to categorize the amount of regressive changes after cytotoxic treatment mostly refer onto the amount of therapy induced fibrosis in relation to residual tumor or the estimated percentage of residual tumor in relation to the previous tumor site (Thies S & Langer R, 2013).

## Measures to avoid / minimize bias

Neither randomization nor blinding will be performed in this study.

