|  |  |  |  |  |  |  |  |  |  |  |  |  |
| **Adverse event collection** |  | x | x | x | x | x | x | x | x | x | x | x |
|  |  |  |  |  |  |  |  |  |  |  |  |  |
| **Patient-Reported Outcome** |  |  |  |  |  |  |  |  |  |  |  |  |
| Quality of Life assessment (FACT-C) | x |  |  | x | x | x | x | x | x |  | x | x |
|  |  |  |  |  |  |  |  |  |  |  |  |  |
| **Patient survival status** |  |  |  |  |  |  |  |  |  |  | x | x |
| **Disease status** |  |  |  |  |  |  |  |  |  |  | x | x |

* Biochemistry tests include: blood urea nitrogen, creatinine, electrolytes, SGPT, SGOT, GGT, alkaline phosphatase, and bilirubin.

** Urine or serum pregnancy test for women of childbearing potential and who are sexually active must be performed at baseline and at least every month during treatment.

¥ Free T4 and TSH must be performed at baseline and at least every 8 weeks during treatment and at end of treatment or 30 days post-treatment safety follow-up.

† PD-L1 expression on Tumor and Immune Infiltrating T cells & CD4+, CD8+ and CD3+ T cell infiltration are determined on baseline biopsy, D10 and surgical resection specimen.

‡ The microsatellite instability (MSI or MMR status) is determined once on either the baseline biopsy or D10 biopsy.

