## Randomization codes and procedures for blinding

Not applicable.

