      - - Will be quantified in mm2 in the most abundant tumor-infiltrating area in both, the stroma and the tumor, of the D10 biopsy (continuous variable).
        - After the recruitment of around 5 patients, a cut-off value will be agreed upon and the numerical values corresponding to T cell infiltration (continuous variable) will then be classified as low or high or not applicable (categorical variable).
    - Microsatellite instability (MSI or MMR status):
      - - Will be evaluated once on either the baseline biopsy or D10 biopsy.
        - The MSI predictive markers to be assessed are: MLH-1, MSH-2, MSH-6, and PMS-2.
    - Image of the biopsy is to be provided.
    1. Concomitant medications
    2. Adverse event collection

### 8.2.3. Treatment period: visits 8 to 13

The procedures to be done from week 3 ± 3 days to week 13 ± 3 days (visits 8 to 14), starting D15 are as follows:

- - 1. Physical examination/vital signs/weight
    2. Laboratory tests:
    - Hematology assessments: CBC
    - Blood chemistry: BUN, creatinine, electrolytes, SGPT, SGOT, GGT, alkaline phosphatase, bilirubin
    - Urine or serum pregnancy test for women of childbearing potential who are sexually active
    - Free T4 and TSH
    1. Concomitant medications including mFOLFOX-6 chemotherapy protocol and anti-emetics:
    - Oxaliplatin 85 mg/m2 in a 2-hour infusion
    - Leucovorin 400 mg/m2 over 2 hours
    - 48-hour infusion of fluorouracil 2,400 mg/m2
    1. IMP administration: avelumab 10 mg/kg first administration at D15, then every 2 weeks for 6 cycles
    2. Adverse event collection
    3. Patient-reported outcome: quality of life assessment using FACT-C questionnaire

### 8.2.4. End of treatment visit including study completion and premature withdrawal: visit 13

Besides the procedures to be done at week 13 ± 3 days, tumor markers (CEA and CA 19-9) should be assessed at the end of treatment. Also, at the time patients discontinue the study treatment, a visit should be scheduled as soon as possible, but no later than 14 days from the last day of study medication, at which time all of the assessments listed for the End of Treatment visit will be performed. An End of Treatment eCRF page should be completed, giving the date and reason for stopping the study treatment.

### 8.2.5. Surgery: visit 14

Depending on the patient’s condition and laboratory exams, the procedures to be done 2 to 3 weeks ± 3 days after the last cycle of chemotherapy plus avelumab are as follows:

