### 8.3.2. Centralized assessments

- - 1. Pathology assessment:

| **Assessment** | **Time of assessment** |
| --- | --- |
| PD-L1 expression on tumor and infiltrating immune cells & CD4+, CD8+ and CD3+ T cell infiltration | Baseline biopsy  D10  and  Surgical resection specimen |
| MSI (MMR status) | Once on either the baseline biopsy  or  D10 biopsy |
| TRG | Resected specimen |

Details about the samples preparation and the shipment to the central lab (at AUBMC) are provided in the lab manual.

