## Exploratory endpoints

The exploratory endpoints are:

1. Evaluation of biomarkers CD4+, CD8+ and CD3+ T cell infiltration, and changes in PD-L1 expression. This endpoint aims to demonstrate proof of concept that short-course radiation therapy up-regulates PD-L1 expression and induces immune cell infiltration.
2. Serum markers of inflammation: neutrophil/lymphocyte ratio.
3. Quality of life assessed using FACT-C questionnaire (FACT-C, English version 4 of 16 November 2007 or Arabic version 4 of 03 September 2014).

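### The protocol does not provide for masked reading of the baseline and D10 biopsies, so reader expectation could bias the descriptive before/after comparison of PD-L1 and T cells

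*Protocol*

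**What the plan says.** - **Bias control.** Protocol section 3.3 consists of one sentence: "Neither randomization nor blinding will be performed in this study". Section 6.6, headed "Randomization codes and procedures for blinding", is marked not applicable.
- **Aim.** Section 10.3 says of the biomarker endpoint: "This endpoint aims to demonstrate proof of concept that short-course radiation therapy up-regulates PD-L1 expression and induces immune cell infiltration".
- **Time points.** The footnote to the study flowchart (Table 1) says the markers "are determined on baseline biopsy, D10 and surgical resection specimen". Radiotherapy runs from D1 to D5, and avelumab with mFOLFOX-6 starts at D15.
- **Reading.** Under sections 8.2.1 and 8.2.2, PD-L1 is classed as negative, positive or not applicable, and no positivity threshold is given. For T cells at D10 the rule is "Will be quantified in mm2 in the most abundant tumor-infiltrating area in both, the stroma and the tumor, of the D10 biopsy". How that area is chosen is not stated. A low/high cut-off is to be agreed after about 5 patients have been recruited.
- **Who reads.** Section 8.3.2 lists these reads as centralized: "Details about the samples preparation and the shipment to the central lab (at AUBMC) are provided in the lab manual".
- **Standing and analysis.** Section 2.2 speaks of exploring changes. Section 3.2 lists the biomarkers as a secondary endpoint and section 10.3 as an exploratory one. Section 12.1 plans means with standard deviations or frequency distributions for exploratory variables.

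**The concern.** The aim has a declared direction, and there is no control arm. The within-patient contrast between baseline and D10 is the only one that isolates radiotherapy, because all drug treatment begins after the D10 biopsy. A reader who knows that a slide is post-radiotherapy, and who knows the hypothesis, may resolve borderline PD-L1 calls upwards or search harder for a dense field. Such a shift acts in the same direction as the effect sought, and the recorded scores alone would not reveal it.

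At stake is the credibility of the proof-of-concept statement. Section 17 lists the D10 sigmoidoscopy and biopsy as a trial-specific procedure, so patients undergo an invasive step largely for this comparison. Being a single-arm trial explains why treatment is not blinded. It is no reason to leave slide reads unmasked.

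**Working it through.** **1. The plan's own figures.** The protocol gives no effect size, variance, error rate or power for the biomarker change, so there is nothing to reproduce for this endpoint. The pCR design does reproduce:

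- Early stopping at a pCR rate of 16%: P(X ≤ 2 | n = 13, p = 0.16) = 0.6537, as stated in section 4 (65.37%).
- Rejection probability, summing P(X1 = x)·P(X2 ≥ 10 − x | 23, p) over x ≥ 3: 0.0433 at p = 0.16 (nominal 0.05) and 0.8008 at p = 0.35 (stated 0.8).

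None of these calculations uses a PD-L1 or T-cell read.

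**2. The text side by side.**

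- Section 10.3 wants a rise demonstrated.
- Sections 8.2.1 and 8.2.2 leave two steps to judgement: the PD-L1 call and the choice of field. Once a field is fixed, the cell count leaves less room.
- Section 3.3 makes no exception for readers.
- No passage mentions coded slides, random reading order, masking to time point or a second reader. Section 8.3.2 cites the lab manual only for sample preparation and shipment.

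**3. Illustration on assumed inputs.** None of these values comes from the documents, except that 36 pairs borrows the pCR analysis target. Assume no true change in PD-L1. Let N be the share of truly negative tumours (0.5 to 0.9), e = 0.05 the random error at each read, and b the extra chance that a truly negative tumour is called positive at D10.

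- Read negative then positive: U = N(1 − e)(e + b) + (1 − N)e(1 − e)
- Read positive then negative: D = N·e(1 − e − b) + (1 − N)(1 − e)e
- Average apparent rise: U − D = N·b, since the error terms cancel.

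With N = 0.7 and b = 0.20: U = 0.7×0.95×0.25 + 0.3×0.05×0.95 = 0.1805. D = 0.7×0.05×0.75 + 0.3×0.95×0.05 = 0.0405. The difference is 0.14, or 14 percentage points.

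Over b = 0.10 to 0.30 and N = 0.5 to 0.9, the average apparent rise runs from 0.5×0.10 = 5 points to 0.9×0.30 = 27 points. It does not depend on the number of pairs.

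The protocol plans no test here. If someone nevertheless applied a two-sided 5% exact sign test to 36 pairs, the chance of declaring a rise would be:

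| Share truly negative | b = 0 | b = 0.10 | b = 0.20 | b = 0.30 |
|---|---|---|---|---|
| 50% | 0.2% | 3.4% | 14.7% | 33.8% |
| 70% | 0.2% | 6.8% | 29.6% | 59.3% |
| 90% | 0.2% | 11.7% | 46.7% | 79.7% |

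**4. Is masking feasible?** The reads are already central. No eligibility criterion in section 5.2 uses PD-L1, T cells or MSI, so holding the baseline read until D10 tissue arrives delays no entry decision.

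**The case against.** The strongest reply is that section 3.3 pairs randomization with blinding in an open-label single-arm study, as does section 6.6. The ordinary meaning is blinding of treatment. Neither section mentions slides or readers, and the lab manual, which might cover specimen coding, is not at hand. A reader might infer that the protocol forbids masked reads, or that the central pathologist is known to see the time point. The text supports neither as a stated fact. What it supports is narrower: an unqualified sentence saying no blinding, and no provision anywhere for masked reading. That narrower statement stands.

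Second, the comparison is modest in standing: an objective worded as exploration, an endpoint also labelled exploratory, and a descriptive summary. This limits the consequence, but a biased frequency remains biased when it is only described.

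Third, it is tempting to attach a p-value. For example, with 40 pairs, six one-directional flips (6/40 = 15%) give 2×0.5^6 = 0.031, and five give 2×0.5^5 = 0.063. The arithmetic is right, but no such test is planned, and it assumes no discordance the other way. The table above shows small probabilities at b = 0.10, and no passage indicates how large b is. The pairs may also be far fewer: the protocol puts the chance of stopping after stage 1 at 65.37% if the null rate holds.

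Fourth, masking is imperfect, since D10 tissue is taken about five days after 25 Gy and radiation change may show. This weakens the remedy without removing its value. A masked re-read could also be attempted later if slides or blocks are kept, so the damage need not be permanent. The protocol does not say whether they are kept.

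**Conclusion.** The concern holds as a gap in the design with a cheap remedy. As written, the protocol states that no blinding will be performed and does not provide for masked reading of a judgement-dependent comparison with a declared direction. Reader expectation could therefore bias the reported change in PD-L1 and T cells between baseline and D10. The risk is clearest for the PD-L1 call and the choice of field.

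The size cannot be computed from the documents. The 5 to 27 points are an illustration for the binary PD-L1 call only. They rest on assumed values of the expectation shift and the negative share, and no comparable figure is available for the T-cell counts. The documents do not show that bias will occur, nor that any observed rise would be due to the reader.

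A reader might also want the surgical specimens masked. The documents do not support that: a resection specimen is recognisable, and section 8.2.5 makes the tumour-area T-cell count not applicable when there is a pCR, so its reader must know pCR status. The pCR endpoint, the stage 1 rule and the final test are unaffected.

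**What to change.** - **Section 3.3:** limit the sentence to treatment blinding, and say that masked reading of biopsies is described in section 8.3.2.
- **Section 8.3.2:** state that the central lab codes each patient's baseline and D10 slides and reads them together in random order, masked to time point and clinical outcome.
- **Sections 8.2.1 and 8.2.2:** state the PD-L1 positivity threshold and the rule for selecting the T-cell field, both fixed before any slide is read.
- **Surgical specimens:** no masking is asked for.

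The cost is slide coding at the central lab and a short delay of the baseline read until the D10 biopsy arrives. No additional reader, biopsy or visit is needed. Masking will be incomplete where radiation change is visible, and the report should acknowledge this.
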